#### Measures of early maths skills

Children’s early maths skills were measured with an adapted version of the Number Sense Screener [67]. This instrument assesses aspects of early mathematic ability, namely one-to-one correspondence, number sense cardinality, ordinality and subitizing, which are some of the important mathematical concepts that develop during preschool years [68, 69].

#### Measure of emotional comprehension

The Test of Emotion Comprehension (TEC) was used to quantify the children’s emotional comprehension skills. The test assesses nine domains of emotional understanding: the recognition of emotions based on facial expressions, the comprehension of external emotional causes, the impact of desire on emotions, emotions based on beliefs, memory influence on emotions, the possibility of emotional regulation, the possibility of hiding an emotional state, having mixed emotions, and the contribution of morality to emotional experiences [70]. The TEC has been validated on Italian, Norwegian, Brazilian, Peruvian and Portuguese children [70, 71].

### Composite measures

Three composite measures were used to assess general EF, language ability, and communicative ability. These composite measures were calculated by summing the standardized individual component scores, and then standardizing the resulting sum scores. The EF composite measure consists of the individual DCCS, Flanker, HSKT, and FDS components, the language composite measure consists of the individual PPVT, Predicates, Subordinates and Events components, and the communication composite score consists of the individual TEC, and the scores from a blind rater on communicative skills measured from the video-recordings of the test situation.

### Background measures/covariates

#### Socioeconomic status (SES)

A 10-grade scale of socioeconomic status was estimated on the basis of both of the two caretakers’ annual income and their education level. The annual income of each caretaker was classified on the three-level income scale 1: 0–200,000 SEK, 2: 200000–500,000 SEK, and 3: > 500,000 SEK. Each caretaker’s education level was classified on a four-level scale 1: elementary school only, 2: upper secondary school, 3: vocational education, and 4: college/university education. A composite score on a scale from 0 to 10, consisting of even numbers only, was calculated for each parent p on the basis of their annual income score *Ip* and their education level score *Ep* in the following way:

$$ SESp=\left({\left( Ip+ Lp\right)}^{\ast }\ 2\right)-4 $$

For children living with both caretakers, the mean of both caretakers’ composite scores was used (thereby making it possible for the scale to include odd numbers). For children living with only one of the two caretakers, the score of that caretaker was used.

#### SCDI

The Swedish Communicative Development Inventories (SCDI) was used to assess aspects of the language abilities of the children [72, 73]. SCDI is the Swedish version of the MacArthur Communicative Development Inventories (CDI). The SCDI instrument assesses communicative and language abilities in children aged 8–48 months by means of parental reports. For this study, a preliminary version of SCDI – SCDI III [see [74, 75], for a validation of SCDI III] developed for children aged 30 to 48 months was used. This questionnaire includes questions pertaining to the children’s general language ability, vocabulary, grammatical ability, pronunciation, and meta-linguistic ability. In the assessment of the children’s vocabulary, parents are probed on their children’s word knowledge within the four semantic domains of food, body parts, thought, and emotion. The assessment of the children’s grammatical ability includes questions regarding their use of the past tense, the passive voice, conjunctions, and the use of comparative inflection (e.g., little, more, most). The total number of words that the child knows, as reported by their caregivers, serves as an estimate of the children’s’ vocabulary size (SCDI words). The ability of the children to form the past tense, to use the passive, and to use comparative inflection, as reported by their caregivers, was used as a score of the children’s morphological ability (SCDI morphology).

#### Age

As age can be expected to be highly predictive of all of the outcome measures, the age of the children in months was used as a control predictor.

#### Sex

A number of studies indicate a difference between boys and girls in the 4- to 5-year age span with respect to attention span [76], cooperation and social interaction skills [35, 36, 77], as well as command of language [78]. Sex has also been reported as a variable to consider in behavioural ratings, including hyperactivity, which is more frequently found or diagnosed in boys than in girls [79–81], and emotional difficulties such as phobia and eating disorders, which are more frequent in girls [82, 83]. These differences have not yet been documented in the Swedish preschool population, but sex was included as a control predictor on the basis of the studies mentioned above.

#### Preschool start

Preschool start might have an influence on some or many of the outcome measures. In a review of key studies from Europe, North America and Asia, Burger [83] concludes that an early start in preschool may have positive effects on child development, however, the findings are not conclusive. Loeb et al. [84] showed that academic gains from attending preschool in the context of the Head Start program in the United States are greater for those children who start preschool at the age of 2–3 than at a younger or older age. An early preschool start might either have a positive or negative effect on the children’s development. The age in months at which the children started in preschool was therefore included as a control predictor.

#### Preschool time

It might also be the case that the amount of time the children spend in the preschool has either a negative or a positive influence on their development. Burger [83] concludes that there is not enough evidence to draw conclusions regarding the ideal intensity of preschool participation. The above-mentioned study undertaken by Loeb et al. [84] showed that more hours in preschool led to higher academic gains but had some negative effects on behaviour. In order to investigate the contribution of preschool time in the present study the average number of preschool hours per week was included as a control predictor.

#### Second language

There are studies indicating that speaking a second or more language/s might have a positive effect on EF and inhibitory control [85–87]. Research indicates that bi- or multilingual children have both/all languages activated and potentially competing for selection [88, 89]. The control mechanisms required to inhibit the not targeted languages has been argued to influence and enhance the child’s inhibitory cognitive systems in a broader sense, aiding the individual in cognitive inhibitory functions more generally compared to monolingual children and adults [90]. Children learning more than one language, may, on the other hand, be somewhat delayed in their first language during the first few years of life [91]. The time when a second or third language is introduced affects the child’s results on executive functions tests with an advantage for younger bilinguals over children acquiring their second language at a later age [92]. Whether or not the child at hand speaks a second or third/fourth language (in addition to Swedish as their first language) was therefore included as a control predictor.

#### Swedish-as-L2

A number of children had a foreign language as their first language (L1), making Swedish their second (or perhaps even their third) language. As these children can be expected to be less proficient in Swedish, having Swedish as a second language was included as a control predictor.

#### Known language and/or other developmental disorders

Since all children who could participate in the behavioural testing were seen as eligible for participation in the study, any known/documented language disorder and/or other developmental disorder was included as a control predictor. The presence of developmental difficulties has been shown to significantly predict language development (e.g. [93]).

#### Family history of language disorders

This control predictor indicates whether there is a family history of language disorders, such as dyslexia. Language and literacy disorders are highly heritable and can also influence the child’s home language environment [93, 94].

#### SDQ

The Strengths and Difficulties Questionnaire (SDQ) is a parental report inventory behavioural screening for children aged 2 to 17 years old [95–97] that has been translated into a vast number of languages. The Swedish version targets the ages 3 through 16 and was translated by Smedje et al. [98]. The questionnaire contains 25 questions addressing behaviour in the Difficulties domain such as hyperactivity and attentional issues, behavioural deviations, difficulties with social relations and self-regulation skills concerning emotions. In the Strength domain, the questionnaire measures prosocial behaviour such as generosity, considerateness and the ability to wait for one’s turn. The SDQ has been validated for Swedish children from 6 to 10 years of age [99], which is outside the age span for the sample investigated here (4- to 6-year olds). The test is sensitive enough to distinguish between control and clinical samples, but is better adjusted for boys than for girls in that the majority of behavioural difficulties captured are within the hyperactivity scale, and hyperactivity is more frequently found in boys. The test misses some of the behavioural difficulties more frequently found in girls (e.g. emotional disorders like phobia and eating and anxiety disorders).

Both parental and preschool teacher SDQ assessments were obtained. On the basis of the scoring principles at the youth-in-mind SDQ website http://www.sdqinfo.com/, SDQ scores of prosocial behaviors as well as of total difficulties were calculated both for the parental and preschool teachers. Finally, composite scores consisting of the mean of the parental and the preschool teaching assessments were calculated for use in the statistical analyses.

#### Fidelity

As described in more detail above, fidelity measures in the SEMLA intervention were estimated on the basis of the documentation provided by the preschool teachers. After each session, teachers documented which children had participated actively in the SEMLA activity. For SEMLA, the fidelity score is the standardized number of sessions each child participated in.

In the DIL intervention, fidelity measures were provided both through teacher documentation, and through registration by the Magical Garden software of the number of sessions and amount of time spent playing the game. Teachers documented the number of times each child participated in “the learning body” sessions, and the Magical Garden software recorded the number of times each child played the game and the duration of each session. The fidelity score for the DIL intervention was calculated as the standardized sum of the number of “the learning body” sessions and the number of Magical Garden sessions, weighted with respect to the mean play time of the child.

For participants in the control group, a fidelity score of zero was used. This resulted in a standardized fidelity score with a mean of zero and a standard deviation of 1, zero being treated as a baseline value (i.e., as in the case for the participants in the control group, who did not participate in any intervention activities).

#### ECERS-3

As discussed above, the ECERS-3 consist of several measures of preschool quality relating to the quality of the preschool facilities, the daily routines, the use of language at the preschool, the learning environment, and the way that interactions take place [56]. In the statistical analyses, the standardized means of these individual scores were included as a control predictor at the preschool unit level.

### Statistical analysis

Statistical tests will be conducted in order to test the hypotheses outlined in Table 1. Different tests will be employed to test the hypotheses of each corresponding research question (RQ1 to RQ7). In the following section, the analyses for each corresponding research question are described.

### RQ1 analyses: Intervention effects

For RQ1 hypotheses, mixed effects modelling will be used to test the null hypotheses that there are no intervention effects on each of the respective outcome variables. Mixed effects modelling allows for the inclusion of multiple hierarchically nested random effects, such as children nested within preschool units and preschool units nested within preschools (e.g., [100]). The mixed effects model can thereby account for systematic influences of preschool units or preschools on the outcome variables. The model formula for the RQ1 hypothesis analyses is:

$$ {\mathrm{POSTSCORE}}_{\mathrm{ijk}}=\kern0.5em {\upalpha}_{0\mathrm{jk}}+{\upalpha}_{00\mathrm{k}}+{\upbeta}_1{\mathrm{INTERVENTION}}_{0\mathrm{jk}}+{\upbeta}_2{\mathrm{Y}}_{\mathrm{ijk}}+{\upbeta}_3{\mathrm{PRESCORE}}_{\mathrm{ijk}}+{\upbeta}_4{\mathrm{FIDELITY}}_{\mathrm{ijk}}+{\upbeta}_5{\mathrm{ECERS}}_{00\mathrm{k}}+{\upvarepsilon}_{\mathrm{ijk},}\ {\upvarepsilon}_{\mathrm{ijk}}\sim \mathrm{N}\left(0,{\upsigma^2}_{\upvarepsilon \mathrm{ijk}}\right),{\upalpha}_{\mathrm{j}}\sim \mathrm{N}\left(0,{\upsigma^2}_{\upalpha \mathrm{j}}\right),{\upalpha}_{\mathrm{k}}\sim \mathrm{N}\left(0,{\upsigma^2}_{\upalpha \mathrm{k}}\right) $$

In the models, the *i*th child is nested within the *j*th preschool unit, which in turn is nested within the *k*th preschool.

These models predict the postscore of the given outcome measure for child *i* as a function of the intervention administered at preschool unit *j*, using the control intervention as the baseline category. They also control for the set of background variables Y of child *i*, as well as the prescore measure of child *i*, centered around zero, as well as the fidelity score for child *i*, as explained in more detail above. Further, they control for the total ECERS rating of preschool *k*, thereby taking into account any influence of preschool quality on the outcome variables. Finally, they include individual intercepts α for each preschool *k*, as well as individual intercepts α for each preschool unit *j*, thereby controlling for systematic differences between preschool units and preschools with respect to the outcome variables.

Separate models will be conducted on selective attention, early maths skills and emotional comprehension, as well as on the composite measures of EF, language and communication.

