### RQ5 analyses: Background - outcome relationships

RQ5 hypotheses concern relationships between outcome variables and background variables. These will be tested with mixed effects models with the structure

$$ {\mathrm{SCORE}}_{\mathrm{ijk}}=\kern0.5em {\upalpha}_{0\mathrm{jk}}+{\upalpha}_{00\mathrm{k}}+{\upbeta}_1{\mathrm{Y}}_{\mathrm{ijk}}+{\upbeta}_2{{\mathrm{INTERVENTION}}_{0\mathrm{jk}}}^{\ast }\ {\upbeta}_3{\mathrm{TIME}}_{\mathrm{ijk}}+{\upbeta}_4{\mathrm{FIDELITY}}_{\mathrm{ijk}}+{\upbeta}_5{\mathrm{ECERS}}_{00\mathrm{k}}+{\upvarepsilon}_{\mathrm{ijk},}\ {\upvarepsilon}_{\mathrm{ijk}}\sim \mathrm{N}\left(0,{\upsigma^2}_{\upvarepsilon \mathrm{ijk}}\right),{\upalpha}_{\mathrm{j}}\sim \mathrm{N}\left(0,{\upsigma^2}_{\upalpha \mathrm{j}}\right),{\upalpha}_{\mathrm{k}}\sim \mathrm{N}\left(0,{\upsigma^2}_{\upalpha \mathrm{k}}\right), $$

predicting the outcome scores of child *i* on the basis of the background variables Y of child *i*, the interaction between the intervention at preschool unit *j* and the time of testing (pre vs. post) of child *i*, the fidelity score of child *i*, and, finally, the ECERS-3 score of preschool *k*. These models will also contain individual intercepts α for each preschool *k* and each preschool unit *j*. As these models contain parameters for the Intervention × Time interactions, they too test whether there are any significant intervention effects on the outcome scores. A positive Intervention × Time intervention effect shows that there is a positive effect on the outcome score in the given intervention group over and above any increase in the outcome score from pretesting to posttesting. Crucially, they also show which of the background variables are positively or negatively correlated with the corresponding outcome variables, even when intervention effects and differences between pre- and posttesting are controlled for.

Separate models will once again be conducted on selective attention, early maths skills, emotional comprehension, as well as on the composite measures of EF, language and communication, respectively.

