The weaknesses connected to the project concern implementation of the study across preschools. Different engagement levels have been noted from different practitioners, and although the control preschools were enrolled in a self-evaluative assessment (BRUK) in the hopes of making them feel that they were actively involved in the study, there is a possibility that being assigned to the control condition in and of itself creates a sense of alienation from the project that could affect the outcome. The major obstacle observed throughout the project was, however, the different levels of participation found in different preschools as a result of particular individuals being more or less personally engaged in the tasks. Although this is a problem for a controlled study, it reflects the everyday situation of all educational practices. In the future, ways to measure and handle the “human aspect” of pedagogical reality as an influential factor in its own right need to be addressed. Thorough qualitative analysis of the interaction data from the present project could, in its continuation, contribute to a deepened discussion and knowledge of how we handle this influential but evasive reality.

The analysis methods chosen are ideal for analysing data sets such as the present one. In particular, by using mixed effects modelling it is possible to account for the hierarchical structure of the data, with children nested within preschool units, and preschool units nested within preschools. By including random slopes for each of these levels, the mixed effects models account for systematic variation that might exist between preschools or preschool units. The mixed effects model also allows for the inclusion of independent variables and covariates at different levels of nesting, such as the inclusion of interventions and the ECERS-3 scores on the preschool unit level, together with other covariates at the child level.

The results of the study are limited, containing outcomes from only 432 children of the approximately 500,000 attending Swedish preschools. However, the results carry the seed for a preschool setting based on evidence from a multifaceted investigation including considerations of children’s development through both measurable, quantitative test-scores on general abilities, and fine-grained qualitative analyses of skills not necessarily visible except through in-depth analyses of interactions between children and pedagogues.

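### The RQ1 model, and the RQ2 contrasts built on it, adjust the intervention effect for attendance recorded after randomisation, on a score whose zero has two meanings

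*Protocol article*

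**What the plan says.** Under RQ1 analyses, "mixed effects modelling will be used to test the null hypotheses that there are no intervention effects" on each outcome. The formula contains the intervention (control as baseline category), background variables, the prescore, a child-level fidelity score and ECERS. The accompanying text names the fidelity term: "as well as the fidelity score for child *i*, as explained in more detail above". No RQ1 model without it is described. The power section on RQ1 and RQ2 says the RQ2 comparisons are contrasts of the RQ1 intervention effects, so they inherit the term.

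The Fidelity section describes the score. For SEMLA, "After each session, teachers documented which children had participated actively in the SEMLA activity", and "For SEMLA, the fidelity score is the standardized number of sessions each child participated in". For DIL it is a standardised sum of two session counts, weighted by mean play time. Every control child gets zero. The section reports a mean of zero and an SD of 1, with "zero being treated as a baseline value (i.e., as in the case for the participants in the control group", who took part in no activities.

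The Adherence section lets children opt out at any time. The Discussion names as the major obstacle "the different levels of participation found in different preschools as a result of particular individuals being more or less personally engaged".

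The RQ5 model also contains "the fidelity score of child *i*, and, finally, the ECERS-3 score of preschool *k". Its intervention test is the interaction: "A positive Intervention × Time intervention effect shows that there is a positive effect on the outcome score in the given intervention group". The RQ4 models omit fidelity.

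**The concern.** Attendance arises after allocation, depends on the child's willingness and the staff's engagement, and has no counterpart in the control arm. Randomisation does not balance such a variable. Putting it beside the arm term changes either what the arm coefficient means or what its standard error measures. A single slope is also forced on two different scales, a SEMLA session count and a weighted DIL sum.

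Which problem arises depends on the meaning of zero, and the Fidelity section gives two. In a standardised score, zero is average attendance. In the gloss about controls, zero is no attendance. The RQ1 coefficients and the RQ2 contrasts are the trial's main answers, so both their meaning and their p-values are at stake.

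**Working it through.** **The plan's own figures.** The article gives no figure for the effect of the fidelity term. The nearest is Table 4 (for example, power 0.69 for SEMLA on EF, 0.61 after adjustment). It rests on bootstrapped pilot data that are not shown, so it cannot be reproduced, and nothing in the simulation description ties it to fidelity. It is not used here.

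**Scale of the score.** Allocation is 32, 36 and 32%. If each intervention arm has mean 0 and SD 1 and controls are exactly 0, the whole-sample SD is the square root of the non-control share: √0.68 = 0.82 if control is a 32% arm, √0.64 = 0.80 if it is the 36% arm. The stated SD of 1 therefore holds within the intervention arms only.

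**Reading A: standardised within each arm, controls 0.** The score averages zero in every arm, so it is uncorrelated with the arm indicators and the point estimate stays put. But unit-level attendance absorbs between-unit outcome variance, which shrinks the model's standard error. Centring within the arm leaves chance differences between arms in engagement unadjusted, so the true variance of the contrast does not shrink with it.

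Simulation under a true null: 432 children, 28 units (9/10/9 per arm), 1,500 runs per scenario, REML with a unit intercept, two-sided 0.05. Assumptions not in the document: unit ICC 0.05, pre-post slope 0.6, residual SD 0.8. Here r is the correlation of engagement with the outcome residual, and the unit share is the part of engagement variance lying between units. The preschool intercept and background covariates were left out.

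| r | Unit share | Model SE with fidelity | Empirical SD | Type I error with fidelity | Without |
|---|---|---|---|---|---|
| 0 | 0.3 | 0.124 | 0.126 | 6.7% | 6.7% |
| 0.3 | 0 | 0.118 | 0.125 | 7.5% | 6.9% |
| 0.3 | 0.3 | 0.123 | 0.131 | 7.6% | 5.1% |
| 0.5 | 0 | 0.110 | 0.116 | 7.6% | 5.6% |
| 0.5 | 0.3 | 0.123 | 0.149 | 12.3% | 5.7% |

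These are z tests. With a t reference on 25 degrees of freedom the last row is 10.7% against 4.7%, so a small-sample correction does not remove the gap. Without fidelity the model SE in that row is 0.151, close to the empirical 0.149.

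A second simulation (28 units of 15 children, pre-post correlation 0.7, attendance mean 18 of 24 sessions, SD 4; attendance correlated 0.5-0.7 with unit effects and 0.2-0.3 with child effects) gave no bias, and type I error of 5.6-7.8% with fidelity against 4.5-5.1% without.

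**Reading B: zero means no sessions.** The arm coefficient is then the arm difference extrapolated to zero attendance. Assume sessions have mean 18 and SD 5. Under a true null with prognostic attendance, the coefficient is about −(r × 0.8 / 5) × 18:

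- r = 0.1: −0.016 × 18 = −0.29 (simulated −0.29, rejection 30%).
- r = 0.3: −0.048 × 18 = −0.86 (simulated −0.88, rejection 98%).

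With a true average effect of 0.30 delivered through sessions, the simulated coefficient is 0.00 with fidelity and 0.30 without.

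**RQ5.** Fidelity is one value per child with no time index, so it cannot move a pre-to-post contrast when the child has both tests. Simulated Intervention × Time was 0.293 with and 0.293 without fidelity, SE 0.164 both ways. Across the null scenarios type I error was 0.9-4.4%.

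**The case against.** The strongest defence is that the text points to reading A. Both intervention scores are called standardised and the mean is given as zero. If zero meant no sessions, attendance could not be negative and the mean could not be zero. On reading A the estimate equals the unadjusted one, and the distortion of the standard error needs correlations that the article does not report: the Discussion records uneven engagement, not its relation to outcome. The simulation also omitted some of the model's terms. All of this stands. It limits the size of the point, but a covariate that cannot improve the arm contrast and may corrupt its standard error still has no place in the main test.

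The article also says under Study design that adherence will be taken into account in the analyses. A separate adherence analysis meets that commitment.

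The RQ5 models offer an intervention test that fidelity does not move. That stands too, but RQ5 lies outside the planned false-discovery correction and is not the stated RQ1 test.

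A reader might infer three stronger points that the document does not support:

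- That the RQ1 estimate is badly biased. This needs reading B, which only the baseline gloss suggests.
- That the RQ5 intervention test is spoiled as well. Its coefficient is the interaction, which did not change.
- That exact zeros for controls undo the analyst's blinding. The RQ1 model needs control identified as the baseline category anyway, so this adds little.

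**Conclusion.** The point holds for RQ1 and, through it, for RQ2. The intervention coefficient is adjusted for a post-randomisation score that exists in two of the three arms, and the article does not settle what zero means on that score. On the better-supported reading the estimate is intact, but its standard error is too small when attendance is prognostic and clustered by unit. Under the assumed correlations type I error is about 6-8%, about 12% at r = 0.5 with a unit share of 0.3, and undistorted at r = 0. On the less likely reading the coefficient is not the randomised effect at all. The direction follows from the model; the size rests on assumptions that the article cannot confirm. For RQ5, only the intervention main effect (a pretest difference) or children with incomplete pre/post data could be touched.

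**What to change.** Make the RQ1 models, and the RQ2 contrasts taken from them, primary without the fidelity term, so that the coefficient is the effect as randomised. Report fidelity in a labelled secondary analysis within SEMLA and within DIL, with a separate slope for each arm and no control children. State over which children each score is standardised and what zero means, and correct the SD statement accordingly. Dropping fidelity from RQ5 is optional.

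The cost is one term removed, one secondary model added and a few sentences of definition. No new data are needed. It should be settled before the outcome data are analysed.
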